## Statistical methods

### Sample size calculation

The assumptions used to calculate the number of participants for the study were determined from the article by Constantin et al*.* [14]. In that prospective, randomized, controlled trial assessing the "impact of sophrology on the tolerance of NIV sessions in patients with ARF," the difference in respiratory discomfort between patients treated with sophrology and the control group was 2.8, with a standard deviation of 2.5.

For our study, we considered the same standard deviation but a less optimistic difference for the comparison of the “sensory deprivation” group and the “musical intervention" group. Seventy-eight participants (26 participants per arm) should be included to obtain a power of 80 % to demonstrate a difference of 2 units of respiratory discomfort between the two groups, with an alpha risk of 5 % (bilateral formulation).

Three comparisons will be performed to assess the primary endpoint: a comparison between "musical intervention" and “sensory deprivation," a comparison between "musical intervention" and "NIV alone," and a comparison between "sensory deprivation" and "NIV only." If the three comparisons were each performed with a significance level of 5 %, the overall type I error rate would be far above the nominal level (14 %). To maintain an overall type I error rate of 5 % in a strong sense, we will apply a non-parametric Bonferroni-based chain procedure [32] for the analysis (as explained in the following section on statistical analysis), which implies reducing the significance level of two comparisons at 2.5 %. In order to maintain a power of 80 %, the number of planned participants was increased to 93 in total (31 per arm).

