### Study objectives

The primary objective of the present trial is to assess the hypothesis that a musical intervention administered to patients with ARF in the ICU improves NIV tolerance and thereby their comfort and ventilation parameters after 30 minutes of NIV, in comparison to conventional care.

The secondary objectives are to assess musical intervention effect on respiratory comfort and respiratory and cardiovascular parameters during NIV sessions; on NIV failure; on anxiety and agitation during NIV; anxiety/depression and health-related quality of life; post-trauma stress induced by NIV; and on overall assessment of NIV in terms of discomfort, trauma, and satisfaction.

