#### Primary endpoint

The change in respiratory comfort at initiation and after 30 minutes of the first NIV session will be analyzed in the intention-to-treat population. For each patient, the variation in respiratory comfort will be calculated by the difference between the measurement at “30 minutes” and "before." This change will then be compared between the treatment groups, based on a Student’s *t* test. If the test application conditions are not met, a Wilcoxon test will be applied.

Because three parallel groups are included in the study, three comparisons are possible: "musical intervention" and "NIV only" (comparison 1), "sensory deprivation" and "NIV only" (comparison 2), and "musical intervention" and "sensory deprivation" (comparison 3). These comparisons will be performed in a pre-established hierarchical test procedure (see Fig. 3), in order to maintain the alpha risk of 5 % in a strong sense:Step 1: We will perform comparisons 1 and 2, both at 2.5 % (bilateral) alpha risk.Step 2: In the event of non-significance of the two previous tests, we will stop the test procedure and conclude the negativity of the trial; in the case of statistical significance of both previous tests, we will perform comparison 3 at 5 % (bilateral) alpha risk; in the case of statistical significance of only one of the two previous tests, we will perform comparison 3 at 2.5 % (bilateral) alpha risk.Step 3: If comparison 3 was performed at 2.5 % alpha risk and is significant, the non-significant comparison performed in step 1 may be performed again at an alpha risk of 5 % (Fig. 3).

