Music therapy has shown its beneficial effects on patient anxiety, pain [24], and physiological events (heart rate, blood pressure) either outside [15, 42–44] or inside the ICU [16–20]. These studies showed that music therapy is feasible in the ICU, although only a small proportion of invasively ventilated patients (5.3 %) might benefit from such an intervention [17]. As such, music effects have never been assessed during NIV, a ventilator mode increasingly used in the ICU [45]. Therefore, one may surmise that many more patients will be affected by this intervention. Given that anxiety is one of NIV’s major drawbacks, our aim is to decrease potential stressful feelings that might be induced by NIV with the music therapy. This has been shown in the ICU: Han et al. [18] showed that a single music session significantly decreased anxiety (measured by the Spielberger State/Trait Anxiety Inventory) in patients invasively ventilated, compared to those who did not receive music. Likewise, Chlan et al. showed a significant effect of patient-directed music therapy on reducing anxiety (measured by a visual analog scale) compared with usual care during ICU stays in patients being ventilated [17].

It has been shown that post-ICU symptoms of anxiety, depression, or post-traumatic stress disorder (PTSD), especially in NIV patients [46], might occur up to 90 days after an ICU stay. Unfortunately, these symptoms were not assessed after this time in previous studies of music intervention, and never in NIV patients. In our trial, we plan to evaluate these symptoms and to find if a punctual intervention (i.e., 30 minutes of music intervention during NIV sessions) can diminish such post-ICU symptoms. Short- and long-term assessment of NIV-related PTSD seems necessary to determine the length of action of the interventions being tested.

Chlan et al. evidenced that music administration led to significantly less anxiety and sedation intensity compared to usual care in ventilated patients. But this was not evidenced when comparing usual care to noise-canceling headphones. We therefore decided to build a three-arm trial in order to distinguish the effects of the music and of the isolation of the noise and the light of the ICU. As ICU patients report noise as the main source of discomfort [47], we naturally question in our trial the role of noise isolation and of music in NIV (and ICU) tolerance, and therefore tested the “sensory deprivation” strategy.

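### The 80 % power with 31 per arm is attached to music versus sensory deprivation, a test run only after a significant step-1 result; its overall power depends on an unstated control mean and is about 70 % if sensory deprivation equals control

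*Protocol article*

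**What the plan says.** All references are to the protocol article.

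- **Sample size calculation, the effect.** The planning SD is taken from an earlier trial of sophrology during NIV, where the difference from control "was 2.8, with a standard deviation of 2.5". The present trial keeps the SD and adopts "a less optimistic difference for the comparison of the “sensory deprivation” group and the “musical intervention' group". It first sizes 26 per arm for 80 % power "to demonstrate a difference of 2 units of respiratory discomfort between the two groups", "with an alpha risk of 5 % (bilateral formulation").
- **Sample size calculation, the inflation.** Because the multiplicity procedure puts two comparisons at 2.5 %, and in order to keep 80 % power, "the number of planned participants was increased to 93 in total (31 per arm"). No difference between either active arm and NIV only is given.
- **Primary endpoint (statistical analysis).** Step 1 tests music versus NIV only (comparison 1) and sensory deprivation versus NIV only (comparison 2), each at two-sided 2.5 %. Step 2 tests music versus sensory deprivation (comparison 3) at 5 % if both were significant and at 2.5 % if one was. Otherwise: "In the event of non-significance of the two previous tests, we will stop the test procedure and conclude the negativity of the trial".
- **Study objectives.** The primary hypothesis is that music "improves NIV tolerance and thereby their comfort and ventilation parameters after 30 minutes of NIV, in comparison to conventional care". That is comparison 1.

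**The concern.** The only pair of arms with a stated effect size is the pair that may never be tested. A power calculated for a stand-alone test does not carry over to a test that first needs another test to succeed. Its overall power is the probability that the gate opens and comparison 3 is then significant, and the first of these events depends on how far music and sensory deprivation each lie from control. The plan is silent on both distances.

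Comparison 3 is the reason for having three arms: it separates the effect of the music from that of shutting out noise and light. If its chance of success is below the stated 80 %, the trial is less likely to deliver that separation than a reader would suppose. In addition, no planning difference is stated for the comparison named in the primary objective, so a reader cannot tell which comparison the 80 % covers.

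**Working it through.** **Inputs.** From Sample size calculation: music minus sensory deprivation = 2, SD 2.5, 31 per arm. From Primary endpoint: Student *t* tests, the three steps and their levels. Not in the document and therefore varied: the difference between sensory deprivation and NIV only. *Better* means less discomfort.

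**1. Reproducing the plan's figures (single test, no gate).** Two-sample *t* test, df = 2n − 2, noncentrality = (2/2.5) × √(n/2).

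- n = 26: 0.8 × √13 = 2.88, df 50, two-sided 5 %: power 80.7 % (25 per arm gives 79.1 %).
- n = 31: 0.8 × √15.5 = 3.15, df 60, two-sided 2.5 %: power 80.0 % (30 per arm gives 78.5 %).

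Both 26 and 31 are the smallest n reaching 80 %, so the plan's arithmetic is reproduced exactly.

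**2. Adding the gate.**

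Overall power of comparison 3 = P(comparison 1 or 2 significant at 2.5 %, and comparison 3 significant at its step-2 level).

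The comparisons share arms and are correlated, so the powers cannot simply be multiplied. The steps were simulated with pairwise pooled-variance *t* tests: 1,000,000 trials per scenario for benefits of 0, 0.5, 1.0 and 2.0, and 400,000 for the other rows. Music is 2 units better than sensory deprivation throughout, with 31 per arm.

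| Sensory deprivation vs NIV only | Music vs NIV only | Overall power, comparison 3 |
|---|---|---|
| 0.5 worse | 1.5 better | 53.6 % |
| equal | 2.0 better | 69.7 % |
| 0.5 better | 2.5 better | 78.7 % |
| 0.6 better | 2.6 better | 79.7 % |
| 0.8 better | 2.8 better | 81.3 % |
| 1.0 better | 3.0 better | 82.5 % |
| 2.0 better | 4.0 better | 86.7 % |

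The ungated test at 2.5 % succeeds in 80.0 % of the same trials. As a check on the equality case, a bivariate normal calculation with correlation 0.5 gives 71.2 %, against 81.8 % ungated on the same normal approximation: again a loss of about 10 points.

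**3. Where the loss arises (equality case).** The gate opens in 80.9 % of trials. Given that it opens, comparison 3 is significant in 0.697 / 0.809 = 86 %. The shortfall lies in the 100 − 80.9 = 19.1 % of trials in which comparison 3 is never run.

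**4. The primary objective (equality case).** Music versus NIV only is a difference of 2 tested first at 2.5 %. Its power is 80.0 % at step 1.

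**5. Effect of sample size (equality case).** If all 33 randomised per arm are evaluable, overall power for comparison 3 is 73.5 %, so the drop-out allowance does not close the gap. About 37 evaluable per arm (3 × 37 = 111) would give 80.0 %.

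**The case against.** **The 80 % may be meant for step 1.** The sentence giving 31 per arm does not name comparison 3. It follows the remark that two comparisons are reduced to 2.5 %, and the two always tested at that level are comparisons 1 and 2. Read so, 31 per arm is right for a difference of 2 from control. This reading is reasonable, and the fix below adopts it. But the text never states that difference, and the power it says it keeps is the one just set for music versus sensory deprivation. The wording needs correcting on either reading.

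**The 70 % case is not a planning assumption.** This is true. If music were expected to beat control by the 2.8 seen in the sophrology trial (an inference; the article does not say so), sensory deprivation would be 0.8 better than control and overall power would be 81.3 %. The Discussion does report, of an earlier study in ventilated patients where music lowered anxiety and sedation intensity against usual care, "But this was not evidenced when comparing usual care to noise-canceling headphones". That makes equality worth showing, but does not establish it: the outcome and the ventilation differ, the arm here adds an eye covering, and failing to show a difference is not showing equality.

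**Stronger readings that the document does not support.** A reader might infer that 31 per arm is miscalculated; it is not. A reader might infer that a non-significant comparison 3 would come from an underpowered test; once performed, that test has about 86 % power in the equality case. A reader might infer that the primary objective is underpowered; for a true difference of 2 it keeps 80 %.

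**Conclusion.** The point holds as a misattributed power statement, not as an error of calculation. The 80 % is a property of a single test at two-sided 2.5 %, and the testing order does not guarantee it for comparison 3. The size of the gap depends on an effect the plan does not state: about 10 points if sensory deprivation equals control, about 1 point if it is 0.5 better, essentially none from about 0.6 better, and about 26 points if it is 0.5 worse. The consequence is a lower chance that the trial can separate music from isolation. Control of the type I error is not in question here.

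These figures assume normally distributed changes, a common SD of 2.5, 31 evaluable per arm, a true 2-unit difference between music and sensory deprivation, and the levels given in steps 1 and 2.

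**What to change.** Leave N, the tests and their order as they are, and restate the power by comparison in Sample size calculation:

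1. Say that 31 evaluable participants per arm give 80 % power for comparison 1 (the primary objective), and likewise for comparison 2, each for a true difference of 2 from NIV only (SD 2.5, two-sided 2.5 %).
2. State the differences from NIV only that are assumed for music and for sensory deprivation.
3. Say that the overall power of comparison 3 under the sequential procedure, for a 2-unit difference between music and sensory deprivation, is about 70 % if sensory deprivation equals NIV only and about 80 % or more if it is at least 0.6 better.

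The cost is two or three sentences. One quoted figure becomes less favourable.

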### Total planned sample size

To take into account a potential loss to follow-up of about a 5 % rate for the primary endpoint, we expect to randomize a total of 99 participants (33 per arm).

### Statistical analysis

A flow chart will describe the number of eligible patients and the number of patients actually included (in total and per arm). For each group and at each assessment date, qualitative variables will be described in terms of number and percentage, and quantitative variables in terms of number, mean, and standard deviation. Quantitative variables with skewed distribution will be presented in terms of median and interquartile range (25th–75th percentile).

#### Primary endpoint

The change in respiratory comfort at initiation and after 30 minutes of the first NIV session will be analyzed in the intention-to-treat population. For each patient, the variation in respiratory comfort will be calculated by the difference between the measurement at “30 minutes” and "before." This change will then be compared between the treatment groups, based on a Student’s *t* test. If the test application conditions are not met, a Wilcoxon test will be applied.

Because three parallel groups are included in the study, three comparisons are possible: "musical intervention" and "NIV only" (comparison 1), "sensory deprivation" and "NIV only" (comparison 2), and "musical intervention" and "sensory deprivation" (comparison 3). These comparisons will be performed in a pre-established hierarchical test procedure (see Fig. 3), in order to maintain the alpha risk of 5 % in a strong sense:Step 1: We will perform comparisons 1 and 2, both at 2.5 % (bilateral) alpha risk.Step 2: In the event of non-significance of the two previous tests, we will stop the test procedure and conclude the negativity of the trial; in the case of statistical significance of both previous tests, we will perform comparison 3 at 5 % (bilateral) alpha risk; in the case of statistical significance of only one of the two previous tests, we will perform comparison 3 at 2.5 % (bilateral) alpha risk.Step 3: If comparison 3 was performed at 2.5 % alpha risk and is significant, the non-significant comparison performed in step 1 may be performed again at an alpha risk of 5 % (Fig. 3).

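### After one step-1 success, comparison 3 and the other step-1 comparison can each be tested at 5 %; the planned 2.5 % level and retest condition give away power

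*Protocol article*

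**What the plan says.** The protocol article (Statistical analysis, Primary endpoint) defines three comparisons of the change in respiratory comfort: 1, music versus NIV only; 2, sensory deprivation versus NIV only; 3, music versus sensory deprivation. The test is Student's *t*, with Wilcoxon as fallback. The hierarchy is as follows.

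- Step 1: comparisons 1 and 2, each at 2.5 % two-sided.
- Step 2: stop if neither is significant. If both are, test comparison 3 at 5 %. Otherwise, "in the case of statistical significance of only one of the two previous tests, we will perform comparison 3 at" 2.5 %.
- Step 3: if comparison 3 was tested at 2.5 % and "is significant, the non-significant comparison performed in step 1 may be performed again at an alpha risk of" 5 %.

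The stated aim is strong control at 5 %. The Sample size calculation section calls this a Bonferroni-based chain procedure, "which implies reducing the significance level of two comparisons at" 2.5 %, and raises the number per arm from 26 to 31 for that reason. Fig. 3 is not available, but the text specifies the procedure completely.

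**The concern.** A generic Bonferroni chain splits and passes on alpha as if any combination of the hypotheses could be true together. That is not so here. If music equals control and sensory deprivation equals control, music equals sensory deprivation. Once one equality is false, at most one of the other two can be true, so nothing is left to share alpha between. The 2.5 % level for comparison 3 after one success, and the condition placed on the retest, are then penalties that the 5 % guarantee does not need.

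Comparison 3 matters. The Study rationale and the Discussion give separating music from isolation as the reason for three arms, and the Sample size calculation sets its 2-unit difference on this contrast. If music works and isolation does not, exactly one step-1 success is the expected path, and on that path the plan applies the stricter level.

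**Working it through.** **Inputs** (Sample size calculation; Total planned sample size): difference 2, SD 2.5, power 80 %, two-sided alpha 5 % or 2.5 %, loss about 5 %.

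**The plan's own figures are reproduced.** The two-sample *t* test (noncentral *t*, standardised difference 2/2.5 = 0.8) needs 25.52, so 26 per arm, at 5 %, and 30.99, so 31 per arm, at 2.5 %. Allowing for loss, 31/0.95 = 32.6, so 33 per arm and 99 in total. The stated 14 % error for three unadjusted tests is 1 − 0.95³ = 14.3 %.

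**Error control of the modified rule.** Write H1, H2, H3 for the three equalities. The rule: if comparison 1 or 2 has p ≤ 2.5 %, test comparison 3 and the other step-1 comparison each at 5 %; otherwise stop. Any two of the nulls imply the third, so the number of true nulls is 3, 1 or 0, never 2.

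- Three true: any rejection requires a step-1 success, with probability at most 2.5 % + 2.5 % = 5 %.
- One true: rejecting it requires its own p ≤ 5 %, with probability at most 5 %.
- None true: no type I error is possible.

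This is closed testing with logical restrictions (Shaffer type).

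**No rejection is lost.** Step 1 is unchanged. With two step-1 successes the rules coincide. With one, p ≤ 2.5 % for comparison 3 implies p ≤ 5 %, and a retest at 5 % conditional on comparison 3 is contained in an unconditional one.

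**Simulation.** 400,000 trials per setting, normal data, 31 per arm, SD 2.5, pairwise *t* tests. Effects are the true benefit over NIV only (music, sensory deprivation). Entries are probability of rejection in %, plan → modified.

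| True effects | Comparison 1 | Comparison 2 | Comparison 3 |
|---|---|---|---|
| 2, 0 | 80.2 → 80.2 | 3.6 → 4.3 (true null) | 69.7 → 74.3 |
| 2, 1 | 80.0 → 80.7 | 25.6 → 33.1 | 24.3 → 31.8 |
| 2.8, 0.8 | 98.1 → 98.1 | 21.3 → 23.8 | 81.3 → 86.4 |
| 2, 2 | 80.2 → 84.8 | 80.2 → 84.8 | 3.6 → 4.9 (true null) |

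Family-wise error, %, plan → modified:

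| True effects | Error |
|---|---|
| 0, 0 | 4.56 → 4.56 |
| 1, 0 | 2.57 → 3.34 |
| 2, 0 | 3.61 → 4.31 |
| 1, 1 | 1.96 → 3.53 |
| 2, 2 | 3.59 → 4.94 |
| 10, 0 | 4.99 → 4.99 |
| 10, 10 | 5.00 → 5.00 |

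The Monte Carlo standard error near 5 % is √(0.05 × 0.95/400,000) = 0.03 points. A separate run of 200,000 trials gave 78.7 → 84.4 for comparison 3 at effects 2.5 and 0.5.

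**Reading the first row.** Taken alone, comparison 3 with 31 per arm has 80.0 % power at 2.5 % and 87.3 % at 5 %. Because it is reached only after a step-1 success, the plan delivers 69.7 %. The modified rule recovers (74.3 − 69.7)/(80.0 − 69.7) = 4.6/10.3, about 45 % of that shortfall.

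**The case against.** The strongest reply is that nothing in the plan is in error. It promises strong 5 % control by a named procedure, specifies every step and keeps the promise; a sharper procedure could be called a preference. It is true that this is lost efficiency and not type I error inflation. But the modified rule makes every rejection the plan makes, and sometimes more, under the same guarantee, so no trade-off is left to prefer.

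Four further points stand as limits.

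- Actual error rises under some partial nulls, for example from 3.6 % to 4.9 % for comparison 3 when both arms gain 2. The 5 % bound is kept, but the realised error is not unchanged.
- The primary objective in the Study objectives section is music versus conventional care. Comparison 1 gains almost nothing unless sensory deprivation also works, and the chance of at least one step-1 success is identical under both rules.
- The argument needs nulls in which two equalities imply the third. Equal means (*t* test) and equal distributions (the usual Wilcoxon null) qualify. A null that one arm's value exceeds the other's with probability one half need not. The chain procedure does not depend on this.
- The trial is open-label and the Trial status section says enrollment is ongoing, so the rule cannot be relaxed informally.

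The sample size is not at fault here: the 2.5 % levels it refers to belong to step 1 and remain.

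**Conclusion.** The concern holds. The planned procedure controls error but is stricter than its 5 % strong-control target requires at two places: the 2.5 % level for comparison 3 after a single step-1 success, and the condition attached to the retest. With 31 per arm and SD 2.5, the cost is about 5 to 8 percentage points of power for comparison 3 in the settings tabulated, and about 5 points for comparisons 1 and 2 when both interventions gain 2 units. The error argument is exact for valid pairwise tests of equal means or equal distributions. The power figures also assume normal data, a common SD and the effect sizes shown. The change is worth making because it bears on the contrast behind the three-arm design, though the plan remains valid without it.

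**What to change.** Keep step 1 and replace steps 2 and 3 with wording such as: *If neither comparison 1 nor comparison 2 is significant at 2.5 %, the procedure stops. If at least one is, comparison 3 and the other step-1 comparison are each tested at 5 % (bilateral), independently of each other's result.* Cite closed testing with logical restrictions (Shaffer type), state that the Wilcoxon fallback tests equality of distributions, and redraw Fig. 3.

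The cost is a short amendment and one figure. It must be dated and documented before anyone sees outcome data by arm; after that point the primary rule should stay as written. The 31 evaluable and 33 randomized per arm do not change, because step 1 still uses 2.5 %.
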